### Statistical analysis

The primary analysis will compare the proportion of patients remitted of depressive symptoms at the 12-month follow-up using a mixed-effects logistic regression model in the intention-to-treat sample (including all randomized patients). Treatment condition (intervention versus control) will be treated as a fixed effect. Baseline severity of depressive symptoms will be included as a covariate and variation among patient clusters (treated by the same GPs) will be modeled through random effects. Further binary outcomes will be modeled correspondingly. Continuous outcomes will be analyzed according to the same scheme, but in linear rather than logistic regression models. Item-level missing data in psychometrically sound instruments will be treated in compliance with the corresponding manuals. If no recommendations are available, the expectation-maximization (EM) algorithm will be used to impute up to 30% of missing item responses. Unit-level missing data (patients not providing data for a whole measurement point due to dropping out of the study, for example) will be imputed via the EM algorithm using existing information from the baseline and 6-month follow-up assessments. Further secondary analyses will include analyses in the per-protocol (completer) sample to test the robustness of the primary findings. No interim analysis is planned. Before the start of the analysis, a detailed statistical analysis plan (SAP) will be prepared by the responsible statistician. Intervention-related data are stored and analyzed separately. All analyses will be computed using Stata 12.1. Figure 4 provides a detailed overview of the study design.

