**Methods/Design:**

The study will be conducted as a cluster-randomized controlled trial comparing the development of depressive symptoms in primary care patients who either receive treatment as usual (control arm) or treatment according to the GermanIMPACT model (intervention arm). In two German cities (Freiburg and Hamburg), a total of 60 general practice offices will be selected and randomized. Each general practice office will be asked to enroll five patients into the trial who are 60 years of age or older and who show moderate depressive symptoms in the scope of a diagnosed depressive episode, recurrent depressive disorder, or dysthymia. General practices in the control arm will provide treatment as usual; general practices in the intervention arm will work closely with a specially trained care manager and a supervising mental health specialist. Evidence-based elements of the treatment plan manual include patient education, identification and integration of positive activities into the daily routine, relapse prevention, and training of problem-solving techniques as needed. The intervention period per patient will be one year. Data will be collected at baseline, 6, and 12 months. Primary outcome is the patient-reported change of depressive symptoms (Patient Health Questionnaire, PHQ-9). Secondary outcomes include measures of quality of life, anxiety, depression-related behavior, problem-solving skills, resilience, and an overall economic evaluation of the program.

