### Sample size

The remission of depressive symptoms as measured by the Patient Health Questionnaire PHQ-9 at 12 months’ follow-up will be the primary outcome measure of the study. A randomized controlled trial investigating the effectiveness of the IMPACT program in the United States yielded a remission rate of 25.0% in the intervention group and 8.3% in the control group [19]. Assuming these remission rates in our trial along with a conventional value for the type I error rate (α = 0.05), a two-sided test on inequality of proportions requires 85 patients per arm (170 in total) to detect this effect with a power of 0.8 (type II error rate β = 0.2). Calculations were done with STATA 12.1 [33]. However, in order to account for the hierarchical structure of the collected data due to the cluster-randomized design, it must be considered that patients treated by the same GP are likely to be more similar in terms of treatment response than patients treated by different GPs. Assuming a fixed number of included GPs (30 per arm, 60 in total) and an amount of variance in the outcome explained by differences between physicians rather than between patients (intraclass correlation coefficient of 10%), the factor of the necessary increase in sample size (so-called ‘design effect’) due to the clustered design yields 1.46, increasing the required sample size to a total of 250 patients. This is the number needed for an appropriately powered per-protocol analysis (only completers are analyzed). To compensate for a conservatively estimated 15% loss to follow-up [19, 31], each participating GP will be instructed to include 5 patients in the study, amounting to a total of 300 patients allocated to the trial (150 per arm). The primary analysis will be performed in the intention-to-treat population, that is, all randomized patients will be included. In the intention-to-treat analysis, the higher number of patients is likely to be compensated for by a potential dilution of treatment effects, so that the power will be approximately the same as described for the per-protocol analysis.

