#### Randomization

A cluster-randomized design was chosen over individual patient randomization in order to avoid intervention contamination and logistic complications within the GP offices. Participating GP offices are randomly assigned to either the intervention or the control arm. To prevent foreknowledge of treatment assignment, the allocation of the practices to the study arms will be concealed from research staff, GPs, and CMs until the intervention process is activated in the intervention arm: after obtaining written consent from participating GPs, a research assistant generates a pseudonymized code for each practice and submits this code to an independent statistician at the Department of Medical Psychology in Hamburg. Participating practices are then assigned to the intervention or control group with a 1:1 ratio according to a computer-generated randomization schedule prepared by the statistician (STATA 12.1, procedure ralloc). Block randomization is used with three variable block sizes, with randomization stratified by site. After assignment to the intervention or control group, the pseudonymized practice identifiers and the study arm allocation are returned to the research assistant at the respective study site. This information is then used to enable intervention activation at practices in the intervention arm. The randomization schedule for the two sites, including the pseudonymized codes for the practices and their assignment, remains with the statistician. Study objectives, intervention, and data assessment pertain to the individual patient level.

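### Site, the only stratification factor named, is missing from the listed model terms: the test is slightly conservative if the sites differ, and the cluster should be worded as the randomised practice

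*Protocol article*

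**What the plan says.** **Randomisation (protocol article, Randomization).** The unit is the practice: "Participating GP offices are randomly assigned to either the intervention or the control arm", and "Participating practices are then assigned to the intervention or control group with a 1:1 ratio". The scheme is: "Block randomization is used with three variable block sizes, with randomization stratified by site". No other stratification factor is named.

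**Model (Statistical analysis).** Remission at 12 months is compared by mixed-effects logistic regression in the intention-to-treat sample. Treatment is a fixed effect, baseline severity is a covariate, and "variation among patient clusters (treated by the same GPs) will be modeled through random effects". Other binary outcomes are modelled in the same way, and continuous outcomes by the linear counterpart. A detailed SAP is announced before the analysis starts.

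**Sites (Setting).** Each of the two sites has 30 participating GPs, two care managers of its own and its own data management.

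**Unit names.** The abstract speaks of offices: "a total of 60 general practice offices will be selected and randomized", and "Each general practice office will be asked to enroll five patients into the trial". Sample size speaks of GPs: 60 in total, where "each participating GP will be instructed to include 5 patients in the study", giving 300 patients. The section on securing the target sample size says that additional GPs will be allocated at random, whereas Randomization allocates offices. The description of the treatment triad says that the German GP typically works in an individual office.

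**The concern.** Stratifying by site balances the arms within each city, so a difference in remission between the cities cannot contribute to the difference between the arms. A model without site does not use that balance. It counts the between-city difference as variation among clusters and charges it to the treatment comparison. The estimate is as precise as the design makes it, but its reported standard error is too large. At stake are some power and confidence intervals that are a little too wide, in the primary analysis and in every outcome that follows the same scheme.

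Secondly, the random effect is described through GPs although offices are randomised. If these were different units, the analysis would cluster at the wrong level.

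**Working it through.** **The plan's own figures.** None concerns site, but the sample size chain reproduces. With 25.0% against 8.3%, a two-sided Fisher exact test has power 0.800 at 85 per arm. Then 170 × 1.46 = 248 (stated: 250), and 250/0.85 = 294.1, so 295, which 60 × 5 = 300 covers.

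**Inputs for the check.** From the protocol: 60 clusters, 30 per arm, ICC 0.10, the two remission rates, two-sided 5% level. Assumed: 4 analysed patients per cluster (close to 250/60 = 4.2) and the site odds ratio, for which the documents give nothing.

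**By hand.** For each arm:
- V = [mean over sites of p(1 − p)]/4 × (1 + 3 × 0.10) is the variance of a practice's remission proportion within a site.
- B = (half the site difference)² is what the site adds to the between-practice variance.

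With balance within site, the true squared SE is (V_c + V_i)/30. Without site, the model estimates (V_c + V_i + B_c + B_i)/30.

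*Type I error, remission 10% and 25% by site in both arms.* The site odds ratio is (0.25/0.75)/(0.10/0.90) = 3.
- V = [(0.0900 + 0.1875)/2]/4 × 1.3 = 0.0451
- B = 0.075² = 0.0056
- True SE over reported SE = √(0.0451/0.0507) = 0.943
- Effective critical value = 1.96/0.943 = 2.08, so type I error is about 3.8%.

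Simulations of this scenario gave 3.4% to 3.9% without site, and 5.0% with it.

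*Power, planned rates, site odds ratio 3.* Splitting 8.3% and 25.0% gives 4.4%/12.2% (control) and 15.1%/34.9% (intervention).
- V_c = 0.0243, V_i = 0.0578, B_c = 0.0015, B_i = 0.0097
- True SE = √(0.0820/30) = 0.0523
- Reported SE without site = √(0.0933/30) = 0.0558
- Reported SE with one common site term = √((0.0820 + 2 × 0.0009)/30) = 0.0529. The half-gaps of 0.039 and 0.099 each lie 0.030 from their mean, which leaves 0.030² = 0.0009 per arm.
- Power without site: (0.167 − 1.96 × 0.0558)/0.0523 = 1.10, so 86.5%
- Power with site: (0.167 − 1.96 × 0.0529)/0.0523 = 1.21, so 88.7%

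**By simulation** (60 clusters of 4, stratified 1:1, ICC 0.10 on the latent scale, cluster-level analysis):

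| Assumed site OR | Type I without / with site | Power without / with site |
|---|---|---|
| 1 | 4.3% / 4.3% | 90.2% / 90.1% |
| 1.5 | 4.9% / 5.2% | 90.5% / 90.7% |
| 2 | 4.4% / 5.0% | 89.0% / 90.1% |
| 3 | 3.7% / 5.1% | 87.9% / 89.8% |

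Compare within rows. The 4.3% at odds ratio 1 occurs with and without site, so it is not a site effect. The hand calculation puts the ICC on the scale of proportions, which is why its power level is a little lower; the loss at odds ratio 3 agrees (2.2 against 1.9 points).

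**Larger gaps.** With 5%/15% (control) and 15%/35% (intervention), odds ratios 3.4 and 3.1 and a smaller treatment difference of 15 points, simulated power is 74.7% without site and 78.8% with it.

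**Cluster unit.** Abstract: 60 offices × 5 patients = 300. Sample size: 60 GPs × 5 patients = 300. The two agree only with one GP per office, and then a GP random effect and a practice random effect are the same term.

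**The case against.** The strongest reply is that this is a condensed article with a detailed SAP to come, and that nothing in it excludes site. A reader should therefore not infer that site will be left out of the final analysis. What stands is that the article sets out the primary model term by term and extends that scheme to the other outcomes. As written, those terms do not match the randomisation.

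It is also fair to say that the omission cannot create an excess of false positives, that the effect vanishes if the cities are alike, and that every figure rests on an assumed site difference. All of that stands and limits the size of the point. Both sites use one treatment manual and a narrow PHQ-9 entry range of 10 to 14, so a very large gap is not an obvious expectation. The simulations use cluster-level analyses rather than the planned mixed logistic model with baseline severity, and are indicative only.

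A reader might further infer that the random effect sits below the randomised unit and inflates type I error. If every office enrolled ten patients through two GPs and the whole ICC lay at office level, the design effects would be 1 + 9 × 0.10 = 1.9 (true) against 1 + 4 × 0.10 = 1.4 (modelled). The SE ratio would be √(1.4/1.9) = 0.86 and type I error about 9%. The documents do not support this. Sixty such offices would give 600 patients, not 300, and each office is asked for five. The ICC is defined between physicians, and one GP per office is called typical. That group practices are not expressly excluded does not show that any will enrol through two GPs.

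**Conclusion.** The point holds for site and is modest. Randomisation is stratified by site and the listed model terms omit it. The consequence runs in the conservative direction: type I error of about 4% to 5% instead of 5%, and about 0 to 2 points of power lost near the planned rates, for assumed site odds ratios of 1 to 3. About 4 points are lost in the 5%/15% against 15%/35% scenario, where both site odds ratios exceed 3. Losses near 10 points arise only with gaps such as 5%/25% (control) and 15%/40% (intervention), odds ratios of about 6 and 4, which nothing in the documents suggests. Baseline severity, already in the model, may absorb part of any site difference.

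The cluster unit is a matter of wording. On the stated counts, GP and practice coincide and no result changes. An inflated type I error from clustering at GP level is not a finding of this review.

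**What to change.** 1. Add site (Freiburg or Hamburg) as a fixed effect to the primary model and to all secondary models that follow its scheme, and fix this before the analysis starts.
2. State that the cluster random effect is that of the randomised practice. Use one term for this unit in Sample size, Randomization, the section on securing the target sample size, and Statistical analysis.

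The cost is one recorded binary covariate and one clarified identifier. In a cluster-level comparison, site takes one degree of freedom (60 − 3 = 57 instead of 60 − 2 = 58). With no site difference, simulated power was 90.1% with site and 90.2% without. The treatment odds ratio becomes conditional on site, as it already is on baseline severity and cluster.

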#### Recruitment of patients

Every participating GP is asked to screen his or her patients according to set inclusion and exclusion criteria and to include five patients for trial participation in the GP practice. Patients of the participating GPs who are 60 years of age or older and show moderate depressive symptoms in the scope of a diagnosed depressive episode, recurrent depressive disorder, or dysthymia (International Classification of Diseases, ICD-10, assessment) are eligible for enrollment at the individual level. Symptom severity is measured with the nine-item depression scale of the Patient Health Questionnaire (PHQ-9; inclusion score 10 to 14). Participants must be willing and able to be contacted regularly by the CM via telephone and to participate in a written survey.

For safety reasons and to avoid data contamination due to comorbidity effects, patients meeting any of the following exclusion criteria are excluded from study participation: alcohol or drug abuse, severe cognitive impairment (e.g., dementia), bipolar disorder, psychotic disorder or severe behavioral symptoms, obsessive compulsive disorder, suicidal ideation and other warning signs of suicide as well as active non-pharmacological (or combined) depression treatment by a specialist (e.g., a psychiatrist or psychotherapist) at time of inclusion. Before GPs apply the PHQ-9 questionnaire, potential participants receive oral and written information about the study. If patients agree to participate in the study, both GP and patient sign the informed consent sheet. Patients, GPs, and the corresponding local study center receive a copy of the signed documents. Subsequently, the local study center will send the baseline questionnaire to the patient. Completed questionnaires will be reviewed by the data management team at the local study centers with regard to exclusion criteria, plausibility of the answers, and completeness of the data.

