#### Assessment

Data are collected at baseline (t_0_), after 6 months (t_1_), and after 12 months (t_2_ = end of intervention, primary time of assessment). Patients in the intervention and control group will receive pseudonymous questionnaires by mail and are asked to complete and return them to the GermanIMPACT data management team. Table 2 shows an overview of the outcome measures, instruments, and times of assessment.

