**Intervention group only**					
Evaluation of intervention	–		–		X
Therapy preference questionnaire	X		–		–
Depression (PHQ-9) - additional measures	–	each session	–	each session	–

*Primary time of assessment (t_**2**_) after intervention.

**Linguistic and culture-specific modifications

*Abbreviations:* PHQ-9, the Patient Health Questionnaire; CDI, the Comorbidity Disease Index; GAD-7, the seven-item Generalized Anxiety Disorder Scale; CPG, the Graded Chronic Pain Scale; FIMA, Fragebogen zur Inanspruchnahme medizinischer und nicht-medizinischer Versorgungsleistungen im Alter; EQ-5D, EuroQol Group; RS-13, the 13-item Resilience Scale.

To avoid the loss of data at baseline and follow-up assessments, the assessors will contact patients whose questionnaires are missing by phone in intervals of 10 to 14 days. For patients who choose to discontinue the trial or deviate from the intervention protocol, a final telephone survey will be conducted. The follow-up calls by the assessors follow a standard operation procedure (SOP) that was defined to ensure a structured and systematic procedure in terms of subsequent collection of missing data via telephone. This approach is restricted to items that do not relate to the patient’s psychological background, with the exception of the PHQ-9 as primary outcome. If answers to more than one item in the PHQ-9 are missing, the PHQ-9 will be reassessed completely by the data management team (in this case, other data regarding health status will be declared invalid). Any revision has to be signed by the assessor with their name and date. Only completed questionnaires will be passed on to data entry.

According to the SOP, data will be entered corresponding to the defined coding plan in the EpiData Entry Client (Version 1.4.2; EpiData Manager Version 1.4.2 for data export) [46]. Instead of running a double data entry procedure, the entered data will be completely (100%) checked and, if necessary, corrected by a second person on the data management team. Data export files (Stata Version 12.1 and SPSS Statistics Version 21 [33, 47]) from both study centers will be centrally collected at the study center in Hamburg for statistical analysis.

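### As written, the model for continuous secondary outcomes carries over baseline depression severity as its only baseline covariate and does not name each outcome's own baseline, although those baselines are collected

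*Protocol article*

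**What the plan says.** The Statistical analysis section of the protocol article sets out the primary model for remission at 12 months: a mixed-effects logistic regression with treatment as a fixed effect and random effects for patients of the same GP. One baseline covariate is named: "Baseline severity of depressive symptoms will be included as a covariate". The model is then extended in two sentences. For binary outcomes: "Further binary outcomes will be modeled correspondingly". For continuous ones: "Continuous outcomes will be analyzed according to the same scheme, but in linear rather than logistic regression models". The only stated change is linear for logistic. The same section adds that, before the analysis starts, "a detailed statistical analysis plan (SAP) will be prepared by the responsible statistician"; that document is not available here.

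On timing, the Assessment section says: "Data are collected at baseline (t_0_), after 6 months (t_1_), and after 12 months". Table 2 marks month 0 for GAD-7, pain, EQ-5D, RS-13, depression-related behavior and problem-solving skills.

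**The concern.** The covariate is named as a specific variable, depression severity, and not as the baseline value of whichever outcome is being analysed. An analyst who follows the text would therefore put baseline PHQ-9, and no other baseline score, into the models for anxiety, pain, quality of life, resilience, behavior and problem-solving. A scale's own earlier value is normally its best single predictor. Leaving it out gives up precision that the collected data could supply, and a chance difference between arms in, say, baseline pain then passes largely unadjusted into the 12-month comparison. EQ-5D deserves particular care because the article lists it among the cost-effectiveness measures, and cost-effectiveness is a stated aim of the trial.

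**Working it through.** The article states no power, sample size or correlation for any secondary outcome, so there is no figure to reproduce. Its sample size calculation concerns remission only and does not bear on this point.

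**Inputs from the article.** 300 patients, 150 per arm; 15% loss to follow-up, so 300 × 0.85 = 255 completers; 250 patients in 60 practices for the completer analysis; intraclass correlation 0.10.

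**Assumptions.** r is the correlation of a 12-month score with its own baseline, 0.4 to 0.7. c is its correlation with baseline PHQ-9, 0.1 to 0.4. Adjustment is taken to reduce variance equally within and between practices, so the design effect cancels in the ratio.

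**Step 1: standard error.** The residual variance, as a fraction of the unadjusted variance, is 1 − r² with the own baseline and 1 − c² with baseline PHQ-9. The standard error with PHQ-9 alone, relative to own baseline alone, is √[(1 − c²)/(1 − r²)]:

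| r | c = 0.1 | c = 0.2 | c = 0.3 | c = 0.4 |
|---|---|---|---|---|
| 0.4 | 1.086 | 1.069 | 1.041 | 1.000 |
| 0.5 | 1.149 | 1.131 | 1.102 | 1.058 |
| 0.6 | 1.244 | 1.225 | 1.192 | 1.146 |
| 0.7 | 1.393 | 1.372 | 1.336 | 1.283 |

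The extremes are √(0.84/0.84) = 1.00 and √(0.99/0.51) = 1.39. At r = 0.6 and c = 0.3, √(0.91/0.64) = 1.19. There, 255 completers adjusted for PHQ-9 alone carry the information of 255 × 0.64/0.91 ≈ 179 adjusted for the own baseline.

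**Step 2: power, as illustration.** Take 125 completers per arm, a design effect of 1 + (250/60 − 1) × 0.10 = 1.32, and an assumed effect of 0.3 SD. Power is 0.55 (c = 0.1) to 0.58 (c = 0.3) with baseline PHQ-9, against 0.67, 0.73 and 0.83 with the own baseline at r = 0.5, 0.6 and 0.7.

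**Step 3: chance imbalance.** With 150 per arm and an assumed design effect of 1.4, which is 1 + (5 − 1) × 0.10, the SD of a chance baseline difference is √(2 × 1.4/150) = 0.137 SD, and the 95% limit is 1.96 × 0.137 = 0.27 SD. Left unadjusted, a difference of that size shifts the 12-month estimate by r × 0.27, or 0.11 SD (r = 0.4) to 0.19 SD (r = 0.7), taking baseline PHQ-9 as balanced or unrelated.

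Steps 1 and 3 largely describe the same cost. The r² share of the variance that own-baseline adjustment removes is the share through which chance imbalance acts, so the two should not be added together.

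**The case against.** The strongest reply is that the text is open to another reading. In the primary model the covariate is the outcome's own baseline, because remission is defined on the PHQ-9. Carried over by analogy, the scheme could mean treatment, the outcome's own baseline and a GP random effect, which is what this point asks for. Covariates for each secondary outcome are also commonly left to the SAP, and one is announced. This stands in part: the article does not exclude own-baseline adjustment, and a reader who infers that baseline PHQ-9 was deliberately chosen in its place goes beyond the text. It does not remove the point, because the published sentence states a rule and names one specific covariate. An SAP that followed it literally would carry the weakness forward.

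Other stronger inferences are not supported:

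- **All secondary outcomes lose power.** PHQ-9 score change and response lose nothing. Nor does every instrument have a baseline: the item listed as "Evaluation of intervention" is collected only at month 12, but it is given only in the intervention arm, so no between-arm comparison is affected.
- **Baseline PHQ-9 is nearly useless because of the entry window.** The criterion "inclusion score 10 to 14" applies to the PHQ-9 used by the GP at screening. The baseline questionnaire is mailed afterwards, so its scores may spread more widely.
- **A QALY difference is distorted.** The article names EQ-5D and a resource-use questionnaire but describes no QALY analysis.
- **The estimates are biased.** Chance imbalance is not systematic bias, and its variability is already reflected in the standard error.

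**Conclusion.** The point holds as a weakness in published wording, limited to the continuous secondary scales other than the PHQ-9. Followed literally, the rule gives a standard error between 0% and about 39% larger than own-baseline adjustment would. That range rests wholly on the assumed correlations. The penalty vanishes where baseline PHQ-9 predicts the outcome as well as its own baseline does, and it would reverse if baseline PHQ-9 predicted better, hence a usual rather than a certain loss. No figure stated in the article changes, and the primary conclusion is not at risk.

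**What to change.** State, before the analysis begins, that each continuous secondary outcome measured at month 0 in both arms is analysed in the linear mixed model with its own baseline value as a covariate, alongside the treatment effect and the GP random effect. Say explicitly that the EQ-5D comparison is adjusted for baseline EQ-5D. Baseline PHQ-9 may be kept as a further covariate; with both in the model, little can be lost whichever predicts better.

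The cost is one sentence in the SAP. The data are already being collected, the sample size is unaffected, and fixing the covariate in advance removes a choice that would otherwise be made after the data are seen.
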